#### Motivation toward physical activity and nutrition

Twice a day patients are asked about their motivation toward PA and nutrition over the next few hours: in the morning (between 8am to 10am) and at midday (between 12pm and 2pm). For each behavior, the questionnaire comprised five items corresponding to the TPB and assessing the following constructs: attitudes, both affective (e.g., “In my opinion, doing physical activity for at least 10 minutes in the next few hours would be a source of pleasure”) and instrumental (e.g., “For me, engaging in physical activity for at least 10 minutes in the next few hours would be beneficial for my health”); subjective norms, referring to perceived social approval from family members, significant others, or health professionals (e.g., “For me, doing physical activity for at least 10 minutes in the next few hours would be approved by most of the important people in my life”); perceived behavioral control (e.g., “It would be easy for me to do physical activity for at least 10 minutes in the next few hours”); and intention (e.g., “I intend to engage in physical activity for at least 10 minutes in the next few hours”). Each item uses a 7-point numeric scale to estimate motivation toward the behavior, with threshold values: 1 Not at all – 3 A bit – 5 Quite – 7 Very much. These questions were created following the guide to prepare a TPB questionnaire [50]. To validate these questionnaires, 7 patients with similar profiles to those likely to be included were asked about their understanding of the questions. To avoid repetitions during the study, 5 different versions were created and alternatively presented (see the complete list in the supplementary files).

#### Fatigue

Patients are asked about their fatigue 3 times a day: in the morning (between 8am and 10am), at midday (between 12pm and 2pm) and in the evening (between 6pm to 8pm). The patient answer thanks to the item: “At the moment, I feel tired” with a 7-point numeric scale with threshold values: 1 Not at all – 3 A bit – 5 Quite – 7 Very much.

#### Nutrition

Patients are asked about their dietary intake twice a day: at midday (between 12pm and 2pm) and in the evening (between 6pm and 8pm). The patient are asked: “If you consider that when you are healthy you eat at 10/10, today you ate at?”, and answer through a 10-point numeric scale with: 1 I don’t eat anything – 10 I eat as usual.

#### Physical activity

The PA data are measured via an accelerometer (ActiGraph GT3X-BT), which provides a reliable and valid objective measure [51]. Patients are instructed to wear the device on their nondominant waist all day for the entire data collection period, except during the sleep period. The ActiGraph GT3X-BT accelerometer provides a device-based measure of PA. If patients engage in activities where the monitor could get wet (e.g., swimming, showering or bathing), they are instructed to remove it. The data are recorded in 30-second epochs. Two day-segments were defined: midnight to 1pm for morning PA and 1pm to midnight for afternoon PA.

The PA intensity is graded based on the Euclidean Norm Minus One (ENMO). The objective is to indicate the threshold intensity based on ENMO to separate inactivity from light, light from moderate, and moderate from vigorous PA, respectively. We will use the following cutoff points: 14 for light (threshold.lig) and 70 for moderate (threshold.mod) intensity PA. These cutoff points are based on two studies among older adults: Sanders et al., in a sample of participants aged from 60 to 86 years old, set the cutoff points at 15 for threshold.lig and 69 for threshold.mod [52], and Migueles et al., among participants older than 70 years old (mean equal to 78.7 years old) defined cutoff points as 18 for threshold.lig and 60 for threshold.mod [53].

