**Methods:**

In this project, older patients with a cancer (≥ 70 years old) complete physical capacity assessments, malnutrition identification, and a comprehensive geriatric assessment with G-code. After that, participants engage in a 2-week data collection protocol combining EMA and sensor-based monitoring of behavior. The participants wear an ActiGraph GT3X-BT accelerometer (ActiGraph, LLC) on their nondominant waist to measure physical activity. EMA questionnaires are delivered 3 times per day - morning (between 8am and 10am), midday (between 12pm and 2pm) and evening (between 7pm and 8pm) - via smartphones or computers with the UniQ digital application. Motivational constructs based on the Theory of Planned Behavior are collected in the morning and at midday. Nutritional behavior data are collected at midday and in the evening. Fatigue is collected in the morning, at midday and in the evening. The data analysis strategy shall include Multilevel Vector Autoregressive Models with k-means clustering.

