### Statistical analysis

The objective of our study is to identify clusters based on predictive motivational variables related to PA and nutritional behaviors among older patients with cancer. The analyses to be conducted aim (i) to identify predictors of PA and nutritional behaviors and (ii) to identify groups of patients with similar patterns of relations between motivation and behavior.

We will evaluate the sample’s adherence to and acceptance of this original data collection with descriptive statistics such as the means, medians, and percentages. These measures will allow us to summarize the key characteristics of the dataset.

For the first step, we will use a Multilevel Vector-autoregressive model (mlVAR), as implemented in the R package “mlVAR.”. mlVAR model will be run in parallel for physical activity and nutrition separately. The mlVAR is a multilevel extension of the vector auto-regression (VAR) model, which describes dynamic relationships among variables measured repeatedly over time from multiple subjects [58]. This model has become a popular tool particularly in studies involving psychological variables [59]. In a contemporaneous network, mlVAR identifies relationships between variables over the same time interval. To observe the temporal dynamics between variables in mlVAR, lagged coefficients quantify the auto-regressive effect (one variable on itself) and cross-lagged effect (one variable on another variable). In this temporal network, these coefficients illustrate the predictive relationships between variables over time and identify potential causal relationships. As a hypothetical example, we can observe that intention at time *t* predicts behavior at time *t + 1*, suggesting a directional influence of intention on subsequent behavior over time.

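### The fixed midnight–1pm–midnight physical activity segments are not aligned with the motivation prompts, so the motivation–activity coefficients are diluted or mixed in time

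*Protocol article*

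**What the plan says.** The section Physical activity sets the outcome windows: "Two day-segments were defined: midnight to 1pm for morning PA and 1pm to midnight for afternoon PA". The device records 30-second epochs and is taken off for sleep. Preprocessing data says that the day is segmented with a GGIR argument.

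The section Motivation toward physical activity and nutrition has patients report "motivation toward PA and nutrition over the next few hours: in the morning (between 8am to 10am) and at midday (between 12pm and 2pm"). The intention item shows the horizon: "I intend to engage in physical activity for at least 10 minutes in the next few hours". The length of that horizon in hours is not given.

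Statistical analysis reads two kinds of relation from the mlVAR model. One has no direction: "In a contemporaneous network, mlVAR identifies relationships between variables over the same time interval". The other is lagged. It is introduced with "As a hypothetical example, we can observe that intention at time" t predicting behaviour at t + 1, and is interpreted as "suggesting a directional influence of intention on subsequent behavior over time". The coefficients then feed the k-means step, and Creation of an intervention uses the resulting profiles to choose behaviour-change techniques.

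On the time grid, the abstract says "EMA questionnaires are delivered 3 times per day". Motivation is asked at the first two occasions and dietary intake at the last two. No section says which PA segment carries which time index.

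**The concern.** An intention score can predict only activity that comes after it, and the item itself limits the prediction to the hours just ahead. The PA windows are set by the clock and ignore when the patient answered. Activity before the answer may even have shaped it: a patient who has already walked may report a higher or a lower intention for the next hours. If that activity is summed into the outcome, a coefficient read as motivation driving behaviour may partly be behaviour driving motivation.

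The first aim is to find motivational predictors of PA, and the second clusters patients on those coefficients. With 40 patients planned and at most 14 × 2 = 28 motivation occasions each, person-level coefficients have little signal to spare.

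**Working it through.** The plan gives no figure of its own here, so the check is interval arithmetic on the stated clock times.

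**Inputs from the article.** Morning segment 00:00–13:00 (13 h); afternoon segment 13:00–24:00 (11 h). Prompts answered at p, between 08:00 and 10:00 or between 12:00 and 14:00. Fourteen days of collection.

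**Assumptions.** Waking at w, between 06:00 and 08:00. The next few hours last h = 2 to 5 h.

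**1. Activity before the morning answer.** By the clock, the share of the segment before the answer is p/13: 8/13 = 62% to 10/13 = 77%. Because the device is off during sleep, waking time is the fairer base: (p − w)/(13 − w).
- Wake 08:00, answer 08:00: 0/5 = 0%
- Wake 07:00, answer 08:00: 1/6 = 17%
- Wake 07:00, answer 09:00: 2/6 = 33%
- Wake 06:00, answer 10:00: 4/7 = 57%

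**2. The 1pm cut.** An answer at 12:00 has its first hour of following activity credited to the morning. An answer at 14:00 comes after 1 h of the afternoon segment, 1/11 = 9% of it. The misplacement is at most 1 h in either direction.

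**3. Same-row layout** (morning PA shares a row with morning motivation, so lag-1 goes to the next segment).
- Gap from prompt to lagged window: 13 − p = 3 to 5 h (morning); 24 − p = 10 to 12 h (midday, overnight).
- Share of the horizon inside the lagged window, morning: max(0, p + h − 13)/h. This is 0% for h = 2 or 3, at most 1/4 = 25% for h = 4, and at most 2/5 = 40% for h = 5.
- Midday: 0% throughout, since the latest end is 14 + 5 = 19:00, before midnight.
- With 28 rows there are 27 consecutive pairs, 14 within a day and 13 across a night.

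Here the relation of interest falls mainly in the contemporaneous network, which has no direction and, for the morning, includes activity before the answer.

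**4. Next-occasion layout** (morning PA stored at midday, afternoon PA in the evening).
- Morning: min(h, 13 − p)/h of the horizon is covered, from 3/5 = 60% to 100%.
- Midday: from (2 − 1)/2 = 50% (answer at 12:00, h = 2) to 100%.

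The relevant hours are not skipped, but the shares in step 1 apply in full to the morning outcome. An autoregressive term adjusts for the previous segment, not for earlier activity within the same one.

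**5. Illustration of size.** The simulation had 2,000 patients, 14 days and waking hours 07:00–22:00. Hourly noise was independent with SD 1, and intention shifted activity by 0.5 per SD in each of the 3 h after the answer and at no other time. Autocorrelation of intention was 0, 0.3 or 0.6. All of these are assumptions, and the results are plain correlations, not mlVAR coefficients.

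| PA outcome paired with intention | Morning | Midday |
|---|---|---|
| 3 h after the answer | 0.66 | 0.65–0.66 |
| Stated segments, next-occasion layout | 0.52–0.55 | 0.39–0.41 |
| Stated segments, same-row layout, lag-1 | −0.01 to 0.24 | 0.00 to 0.33 |

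The same-row values rise only with the autocorrelation, so they reflect carry-over of intention and not the effect built in.

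**The case against.** The strongest reply is that the article fixes no row layout. The step from t to t + 1 is labelled hypothetical, and three occasions a day are described. Dietary intake is recorded one occasion after each motivation prompt, and the PA and nutrition models run in parallel. That fits the next-occasion layout, under which the hours after each prompt are largely captured. Layout and overnight lags are also details that an article may leave to a fuller protocol or SAP. This stands. A reader might infer that lag-1 necessarily jumps over the hours the items ask about, but the article does not support that; it follows under the same-row layout only. Nor do skipping and contamination act together: a lagged window that skips opens after the prompt, and an outcome that contains earlier activity skips nothing.

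It is also fair that the afternoon segment precedes the answer only for replies after 1pm, by at most 1 h, and that 1pm is the midpoint of the midday window. The midnight start adds little, since the device is off during sleep.

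The size depends on assumptions. A standardised slope would shrink by √(1 − share), between 1.00 and √(3/7) = 0.65, only if hourly PA is independent. An unstandardised slope is not biased by unrelated noise in the outcome, only made less precise, and the article specifies no scaling. That defence fails if earlier activity influences the answer.

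What the reply does not remove is that the segment boundaries are a stated choice, and neither layout gives a clean outcome after the answer at both prompts.

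**Conclusion.** The concern holds as a misalignment of the PA segments with the prompts. It rests on stated clock times for two facts: the morning segment always opens before the morning answer, and the 1pm cut misplaces up to 1 h around the midday answer. The waking share of 0–57% depends on waking between 06:00 and 08:00. The lag-1 gaps of 3–5 h and 10–12 h depend on the same-row layout.

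A reader might go further and say that the coefficients do not measure the motivation–PA relation at all. That is too strong. Under the next-occasion layout the midday pairing is diluted by a long window and the morning pairing is contaminated, but both still carry signal. The defensible conclusion is that the coefficients entering the clustering are diluted or mixed in time under either layout, and should not be read as directional without a re-cut.

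**What to change.** For the predictive PA model, replace the two clock segments as follows.

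- **Windows.** Re-cut the 30-second epochs into two non-overlapping windows: from the morning answer to the midday answer (2 to 6 h long), and from the midday answer to a fixed end such as the evening prompt. Ending at 6pm, the second lasts 4 to 6 h. The abstract opens the evening prompt at 7pm while Fatigue and Nutrition say 6pm, so the end time must be stated. Because lengths differ, express PA per worn hour.
- **Missing answer times.** The article does not say that UniQ stores response times. If it does not, or if a prompt is missed, start the windows when the prompt window closes (10am and 2pm) and end the morning one at the midday prompt.
- **Indexing.** Store each window so that lag-1 pairs a motivation score with the PA that follows it, and exclude overnight lags.
- **Adjustment.** Include PA before the answer. For the midday answer this is the preceding window; for the morning answer it is PA from first wear to the answer.
- **Sensitivity.** Keep the two-segment version as a sensitivity analysis.

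The cost is plan wording and a GGIR reprocessing step. The downside is shorter windows with somewhat noisier PA, and the fallback leaves activity between 12 and 2pm out of both windows when neither answer time is available.

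### The ENMO cut-points 14 and 70 fall outside both pairs of values on which the article says they are based

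*Protocol article*

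**What the plan says.** The Physical activity subsection of Outcomes measures grades intensity by ENMO, from a waist-worn accelerometer recorded in 30-second epochs. It fixes the thresholds: "We will use the following cutoff points: 14 for light (threshold.lig) and 70 for moderate (threshold.mod) intensity PA". It then gives their origin: "These cutoff points are based on two studies among older adults". The first study, in participants aged 60 to 86, is reported to have "set the cutoff points at 15 for threshold.lig and 69 for threshold.mod". The second, in participants older than 70 (mean 78.7 years), is reported to have "defined cutoff points as 18 for threshold.lig and 60 for threshold.mod".

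The article gives no rule that leads from these two pairs to 14/70, and no other section mentions the cut-points. The Statistical analysis section calls the behaviour entering the mlVAR model simply physical activity. It does not say whether that means light time, moderate time, total active time or mean acceleration.

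**The concern.** Thresholds taken from two published calibrations would be expected to equal one of the pairs or to lie between them. Here each value lies beyond both sources, and in opposite directions: the light threshold is lower than either and the moderate threshold is higher than either. The stated figures and the stated basis therefore disagree. This is a contradiction within one paragraph, not a detail left to a fuller document.

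Physical activity is one of the two behaviours modelled. The mlVAR coefficients feed the k-means clustering, and the article plans to use the resulting clusters to assign new patients to tailored intervention content. Any activity summary classified by these cut-points carries the choice forward into those steps.

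**Working it through.** **Inputs**, all from the Physical activity subsection. No unit is stated, so I assume that the three pairs share one.

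| Pair | Light | Moderate | Width of light band |
|---|---|---|---|
| Chosen | 14 | 70 | 70 − 14 = 56 |
| Source aged 60 to 86 | 15 | 69 | 69 − 15 = 54 |
| Source older than 70 | 18 | 60 | 60 − 18 = 42 |

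**Step 1. Can 14/70 be reproduced from its sources?** No.
- Adopting either pair gives 15/69 or 18/60.
- The arithmetic mean is (15 + 18)/2 = 16.5 and (69 + 60)/2 = 64.5. The geometric mean is √(15 × 18) = 16.4 and √(69 × 60) = 64.3.
- Any weighted average with weight w between 0 and 1 has light = 15w + 18(1 − w), which lies in 15 to 18, and moderate = 69w + 60(1 − w), which lies in 60 to 69. Since 14 < 15 and 70 > 69, no weight works.
- Rounding to the nearest ten could turn 69 into 70, but no such rounding turns 15 into 14.

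**Step 2. Direction.** The light band [14, 70) contains both [15, 69) and [18, 60). The region from 70 upward lies inside the regions from 69 and from 60 upward. So on any data set, light time is equal or higher, and moderate-or-higher time equal or lower, than under either source. This needs no distributional assumption.

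**Step 3. Distance.**
- Against 15/69: 1 unit at each boundary; width ratio 56/54 = 1.04.
- Against 18/60: 4 units (14/18 = 0.78, or 22% lower) and 10 units (70/60 = 1.17, or 17% higher); width ratio 56/42 = 1.33.

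**Step 4. Illustrative size.** The article gives no ENMO distribution. Assume that epoch ENMO is exponential with mean m. Then the share of moderate-or-higher time is exp(−b/m) and the share of light time is exp(−a/m) − exp(−b/m), where a and b are the light and moderate cut-points.

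The ratio of moderate-or-higher time, chosen pair to source, is exp(−1/m) against 15/69 and exp(−10/m) against 18/60. Example for light time at m = 15: chosen 0.3932 − 0.0094 = 0.3838; 15/69 gives 0.3679 − 0.0101 = 0.3578; 18/60 gives 0.3012 − 0.0183 = 0.2829.

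| m | Moderate+ vs 15/69 | Light vs 15/69 | Moderate+ vs 18/60 | Light vs 18/60 |
|---|---|---|---|---|
| 15 | −6.4% | +7.3% | −48.7% | +35.7% |
| 20 | −4.9% | +5.8% | −39.3% | +30.7% |
| 30 | −3.3% | +4.7% | −28.3% | +28.2% |

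**Step 5. Sensitivity to the assumed shape.** With a lognormal distribution (median 8, 15 or 25; log-SD 0.8, 1.0 or 1.2), moderate-or-higher time is about 2-5% lower and light time about 5-12% higher against 15/69. Against 18/60 the figures are about 16-43% lower and 28-60% higher. The pattern is the same: a small shift against one source, a substantial one against the other.

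**The case against.** The strongest reply is that 14/70 is, in practice, 15/69 with one unit moved at each end, and that the large percentages arise only if 18/60 is the benchmark. That stands as far as size goes, which is why both comparisons are shown. It does not remove the mismatch, since the article names both studies as the basis and the chosen values lie beyond both.

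A second reply is that saying values are based on two studies does not promise an average, and that a fuller protocol may hold the rule. That is possible, and the fix allows for it. But the article states both the numbers and their basis, and no combination of the kind a reader would expect connects them.

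Three stronger readings are tempting and are not supported:

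- *That a high moderate threshold in inactive patients removes the within-person variation that the mlVAR model needs.* This requires moderate time to be the modelled variable, and the article does not say so. The example motivation items ask about at least 10 minutes of activity with no intensity named. If the variable is total time above the light threshold, the moderate cut-point is irrelevant and a lower light cut-point gives fewer zeros, not more. If it is mean acceleration, neither cut-point matters.
- *That 18/60 is the right pair because its sample was older than 70.* Age is the only sample characteristic reported for either source, and the 60 to 86 sample overlaps the eligibility range of 70 or over. Wear site and epoch length are not reported for either calibration, so suitability for this study cannot be judged from the article.
- *That activity is misclassified in absolute terms.* Higher and lower here are relative to the two cited pairs, not to true activity.

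**Conclusion.** The point holds as an internal contradiction: the thresholds that the article fixes cannot be obtained from the sources it names by adopting or averaging them. The direction of the resulting shift is certain for light time and for moderate-or-higher time. For moderate time with an upper limit, it also assumes the same vigorous cut-point under each pair; the article speaks of thresholds "to separate inactivity from light, light from moderate, and moderate from vigorous PA, respectively" but gives no vigorous value.

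The size depends on the comparison and on the assumed distribution, so the percentages in the working are illustrations, not estimates for this cohort. They suggest a probably minor shift against 15/69 and one large enough to matter against 18/60. The consequence for the mlVAR coefficients and the clusters cannot be computed from the article; any summary classified by these cut-points may be affected. Confidence is high for the mismatch and low for its downstream effect. It should be corrected before the accelerometer data are processed.

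**What to change.** Replace 14/70 with one of the two cited pairs, unchanged. Before choosing, confirm from the calibration papers that the pair's wear site and epoch length match waist wear and 30-second epochs. Run the other pair as a sensitivity analysis and report both. If 14/70 has a genuine separate derivation, keep it and correct the sentence on its basis so that it states that derivation.

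The cost is two GGIR parameters and one extra run on stored raw data. No new data are needed. If the pair is changed, results will differ from any preliminary run made with 14/70.

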### Preprocessing data

To analyze the data of ActiGraph GT3X-BT, we will use the GGIR R-package [54]. This package is useful for quantifying the PA with precision by processing multiday raw accelerometer data. The term raw refers to data expressed in m/s^2^ or gravitational acceleration. We use the “qwindow” argument of GGIR to specify whether and how to segment the day for day-segment specific analysis.

Missing data will be imputed via the Kalman filter for both the accelerometer and EMA data. The Kalman filter is a dynamic imputation method that estimates missing values in repeated measures by using both past and present information, accounting for temporal patterns and measurement noise to produce plausible and consistent data over time. The Kalman filter is a popular method for data imputation in time series data, especially those recorded by wearable technology [55] and in EMA conditions [56]. Depending on the characteristics of the dataset, a threshold for acceptable missing data will be established to retain as many valid cases as possible without compromising data quality and to ensure sufficient temporal information per individual. Although the Kalman filter can impute missing values under the assumption of temporal continuity, a minimum amount of observed data is necessary to reliably capture intra-individual dynamics [57].

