However, the TPB has been criticized for its fluctuating prediction of behavioral intentions. Indeed, the designs used are often based on a limited number of measures, failing to consider the temporal fluctuation of perceptions and intraindividual variability [18]. In response to these methodological limitations, repeated-measures methods are relevant to assess the relationship between intentions and behavior on a daily basis [23, 24]. In particular, intentions can vary according to the time of day, reflecting the dynamics of motivational variables [24]. As a result, repeated-measures methods are deemed effective to estimate TPB variables and the intention-behavior gap, as they identify the contexts most conducive to a translation of intentions into action [23].

Ecological Momentary Assessment (EMA) involves repeated sampling of behaviors and experiences, which could consider the temporal fluctuation of perceptions in the subject’s natural environment [25, 26]. The EMA aims to minimize recall bias, maximize ecological validity, and allows the study of microprocesses that influence behavior in real-world contexts. This data collection method is suitable for measuring TPB variables and could improve their predictive ability. Older adults constitute a population particularly amenable to EMA research [27], with high compliance rates (around 80%) [25, 28]. Collecting repeated measures in real time within a naturalistic environment, like wearables technologies and EMA [27], is crucial for a better understanding of the behaviors for this specific population [29]. By improving the observability and feasibility of the components of an intervention, it becomes possible to develop effective, individualized interventions that consider the singularity of individuals and their situation. With the aim of developing an optimal behavior-change intervention for elderly cancer patients, further research is needed to understand the mechanisms of action on PA and nutritional behaviors.

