### Patient selection

Recruitment is anticipated to be completed by April 2026, with the aim of enrolling 40 patients in total. The patients considered for inclusion are those who come for their oncogeriatric care at the Cancer Institute of Montpellier (ICM) which is referral centre in France. If patients are eligible, the study is proposed to them by the investigator. Patients have to meet the following inclusion criteria: being aged 70 or over, having cancer (solid tumors, all sites), having a Geriatric 8 (G8) score ≤ 14, being inactive, i.e., not meeting recommended PA levels of 150 min per week at moderate intensity, providing informed, written and expressed consent and having a social security affiliation.

The exclusion criteria are as follows: known presence of brain metastases, inability to participate in digital platform or physical tests, inability to eat orally, contraindication or inability to engage in PA, inability to follow up regularly for psychological, family, numerical, social or geographical reasons and lack of liberty or under protective custody or guardianship.

This research will be conducted in accordance with the French Public Health Code, the Good Clinical Practice and the Declaration of Helsinki. This study has been registered on clinicaltrial.gov (NCT06445140). This research project has been approved by the national ethics committee (Comité des Personnes Nord Ouest III, accepted on 30 May 2024) and the “Agence nationale de sécurité du médicament et des produits de santé” (ANSM, French National Agency Authority for the Safety of Health Products) has been informed (19 June 2024). Written informed consent was obtained from all participants prior to inclusion in the study. Data will be securely stored using EasyMedStat software.

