## Discussion

### Expects findings

This study aims to identify clusters based on predictive motivational variables related to PA and nutritional behaviors among older patients with cancer, via repeated measures. First, sufficient patient participation and adherence to the protocol are expected, with a good compliance completion rate for EMA and Actigraph GT3X-BT wear. Compliance was considered good if at least 70% of the planned EMA measures were completed across the study period, with fewer than 30% of missed responses. Participants were considered non-compliant if they responded to less than 50% of prompts. Participation and compliance will enhance our knowledge about how EMAs and accelerometers can be used among older adults during cancer treatment. With mlVAR analysis, we will attempt to identify predictors of behaviors based on motivational variables. Second, the analyses should identify groups of patients with similar patterns of relationships between motivation and behavior, by using clustering methods (e.g. k-means) based on the coefficients of the mlVAR model.

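### A single Kalman fill of unstated form before mlVAR biases the motivation-to-behaviour lagged effects when the behaviour series is incomplete, and the missing-data cut-off is left to the dataset

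*Protocol article*

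**What the plan says.** - **Imputation** (Protocol article, *Preprocessing data*): "Missing data will be imputed via the Kalman filter for both the accelerometer and EMA data". The method is described as one that "estimates missing values in repeated measures by using both past and present information". The section does not say whether each variable is filtered alone or motivation and behaviour together. It mentions no repeated draws, no transfer of imputation error and no unimputed analysis.
- **Cut-off** (same section): "Depending on the characteristics of the dataset, a threshold for acceptable missing data will be established to retain as many valid cases as possible". It gives no number.
- **Compliance figures** (*Expects findings*): "Compliance was considered good if at least 70% of the planned EMA measures were completed across the study period", and "Participants were considered non-compliant if they responded to less than 50% of prompts". Neither is linked to entry into the analysis.
- **Use of the data** (*Statistical analysis*): mlVAR is fitted separately for activity and nutrition, and its coefficients are then clustered, for example by k-means.
- **Source of each series** (*Outcomes measures*): motivation is asked in the morning and at midday for 14 days. Intake is an EMA item at midday and in the evening. Activity comes from the accelerometer.

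**The concern.** The lagged coefficients are the substance of both aims: they identify the predictors and they are the input to the clusters. A value filled from a variable's own history carries no trace of what the other variable did. A value filled jointly is built partly from the outcome it will later be used to predict. Either can distort a cross-lagged coefficient, and the model then treats the filled rows as full information.

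The distortion grows with the amount missing, so patients who answer less can appear to have different dynamics. *Creation of an intervention* would offer a technique only where the matching motivational variable emerged as a significant predictor, so an error here passes into the next phase. A cut-off that depends on the dataset also decides which of the planned 40 patients enter both steps.

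**Working it through.** The article gives no effect size, power or precision figure for this analysis, so there is no stated number to reproduce. The check is by simulation.

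**Inputs from the article.** 40 patients; 14 days × 2 motivation prompts = 28 occasions; 27 lag steps each; 40 × 27 = 1,080 steps. The introduction cites EMA compliance of around 80% in older adults, so 20% missing is a natural case.

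**Assumed.** Two-variable VAR(1); autoregression 0.30; motivation-to-behaviour lag 0.25; reverse lag 0.10; between-person SD of coefficients 0.10; innovation correlation 0.3; values missing completely at random; all 28 points treated as consecutive; Kalman smoothing as the fill; person-centred pooled lag-1 regression standing in for mlVAR; 200 replicates. The univariate range covers local-level, local-trend and AR(1) models. The joint fill uses the average VAR parameters.

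**Lagged effect as a ratio to complete data**

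| Missing | Observed pairs | Univariate fill | Joint fill |
|---|---|---|---|
| 20%, motivation only | 1.01 | 1.03–1.05 | 1.22 |
| 20%, both series | 0.99 | 0.84–0.86 | 1.11 |
| 30%, both series | 0.96 | 0.74–0.77 | 1.17 |
| 50%, both series | 1.00 | 0.54–0.58 | 1.33 |

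**Coverage of the complete-data mean by nominal 95% intervals, and mean model SE**

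| Missing | Coverage: pairs | Coverage: univariate | Coverage: joint | SE: pairs | SE: univariate |
|---|---|---|---|---|---|
| 20%, motivation only | 0.92 | 0.91 | 0.59 | 0.036 | 0.035 |
| 20%, both series | 0.95 | 0.74–0.77 | 0.84 | 0.045 | 0.031 |
| 30%, both series | 0.93 | 0.41–0.48 | 0.71 | 0.057 | 0.031 |
| 50%, both series | 0.99 | 0.04–0.12 | 0.32 | 0.107 | 0.029–0.030 |

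With complete data, coverage is 0.88–0.93 and the SE 0.032.

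**Whole prompts missing together.** Two further runs deleted motivation and behaviour jointly (local-level fill, true lag 0.25).
- At 20% missing they gave 0.206 and 0.204: 1 − 0.206/0.25 = 18% and 1 − 0.204/0.25 = 18%.
- At 30% they gave 0.185 and 0.174: 26% and 30%.
- Coverage in the second run was 65% and 29%. Observed pairs there gave 0.247 and 0.244 with 93% coverage.

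With the table's 14–16% and 23–26%, shrinkage is 14–18% at 20% missing and 23–30% at 30%.

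**Usable pairs.** If prompts are lost whole, with compliance c, a patient keeps 27c² pairs: 17.3 at 80%, 13.2 at 70%, 6.8 at 50%. If the two series are lost independently, three values are needed: 27c³ × 40 = 553 at 80% (simulated 555) and 370 at 70% (simulated 372). The SE follows: 0.032 × √(1,080/555) = 0.045. Across both patterns of missingness, observed-pair SEs are 0.038–0.045 at 20% missing and 0.044–0.057 at 30%.

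**Bias or SE?** Model SE over the estimator's own SD is 0.83–0.93 after a univariate fill of both series, against 0.79–0.93 with complete data. For the local-level fill at 30%, an unbiased estimator with SE 0.0312 and SD 0.0377 would cover 2Φ(1.96 × 0.0312/0.0377) − 1 ≈ 0.90. The observed 0.48 is therefore mainly bias.

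**Compliance and clusters.** With compliance varying from 50% to 100% and true effects unrelated to it, mean individual coefficients after the fill were 0.127 below 70% compliance and 0.205 above. The individual correlation with compliance was weak: 0.17, against about 0 for observed pairs.

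**The case against.** **The article does not say the filter is univariate.** Correct. A reader might infer that the plan shrinks the effects; the text does not support a direction. A series-by-series fill shrinks and a joint fill inflates. What stands is that neither tested form is neutral once behaviour is incomplete. The filter's specification alone could be left to the full plan. The choice to fill once and then fit mlVAR is stated here.

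**Activity is measured by the accelerometer, so a missed prompt does not remove behaviour.** This stands. With motivation alone missing, a univariate fill gave 1.03–1.05 times the complete-data value. Other runs gave 0.254, 0.251 and 0.239 at 20%, 30% and 40% missing, with coverage of 88–94%. The activity model with full wear is therefore little affected by such a fill, although the joint fill inflated even there (1.22). The article does expect accelerometer gaps, since it imputes them.

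**The standard errors are not too small for the estimator used.** Largely right. They are small only relative to the information actually observed.

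**The cut-off is ordinary analysis-plan content.** In part. The section ties it to data quality and sufficient data per person. A reader might infer that it will be picked with the clusters in view; the text does not say so. Nor do the 50% and 70% figures already fix it or contradict it, because they define compliance only. What stands is that the article chooses a data-dependent rule, while *Strengths and limitations* allows preliminary silhouette tests, so the order of events matters.

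**Dropping imputation leaves few pairs in poor responders.** True: about 6.8 at 50% compliance with whole prompts lost, about 27 × 0.5 = 13.5 for activity with full wear. mlVAR pools across patients, so this costs precision and does not prevent the fit.

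**Conclusion.** The concern holds in a limited form. A single Kalman fill treated as observed data biases the motivation-to-behaviour lagged effects where behaviour is also incomplete, which mainly means nutrition, and activity during non-wear. Under the assumptions above, the bias is −14 to −18% at 20% missing and −23 to −30% at 30% for a series-by-series fill, and +11% and +17% for a joint one. It is negligible for a series-by-series fill with only motivation missing. Undercoverage comes from this bias more than from the standard errors, which stay at about 0.030 as if nothing were missing.

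It is possible, but not shown to be likely, that clusters will sort patients by compliance; the association found was weak. The sizes depend on the assumed VAR parameters, on pooled regression in place of mlVAR, on smoothing where the article speaks of past and present information, and on missingness at random. Missingness linked to fatigue was not examined, and observed pairs are not immune to it. The threshold is a secondary point, and alone would be closer to a request for detail.

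**What to change.** 1. Make the primary mlVAR fit on observed lag pairs without imputation. Alternatively, estimate the dynamic model for motivation and behaviour with the state-space filter inside the likelihood.
2. Keep the Kalman-filled run as a sensitivity analysis, and state whether its filter is univariate or joint.
3. Set the missing-data threshold before any lagged coefficient or cluster is seen, for example as a minimum number of observed lag pairs per patient. Repeat with an alternative cut-off, such as the 50% or 70% compliance level in *Expects findings*.
4. Report EMA compliance by cluster.

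The change is one of wording and less preprocessing. The price is wider standard errors (0.038–0.045 at 20% missing and 0.044–0.057 at 30%, against about 0.030 after the fill) and fewer usable pairs in patients with low compliance. Their individual coefficients will be pulled towards the group mean, which is a further reason to show compliance by cluster.
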